## Methods/design

The Human Research Ethics Committee at the University of Western Sydney provided ethical approval for this cluster-randomized controlled trial. The study was conducted in Independent and Catholic schools in Sydney, New South Wales, Australia during 2011. Ten schools were identified using publicly available listings, and invited via telephone and email through publicly available contact details. The first five schools whose principal provided consent were included in the study. Once consent was also received from department heads and teachers of Year 8 PE classes, the research team met briefly with the students to provide basic information about the study. At this time, information sheets and consent forms were distributed to students. Students who were unable to participate in PE classes were not eligible to participate in the study. All other Year 8 PE students who returned signed parental consent forms and provided personal assent were allowed to participate in the study. Students who did not return consent forms still participated in the lessons alongside their peers, but did not wear accelerometers, or complete questionnaires.

Figure 2 provides a summary of the study design, a cluster-randomized controlled trial with four study arms. To begin, a familiarization session was held during a PE lesson. During this lesson, students wore an accelerometer and teachers wore a microphone attached to their shirt that connected wirelessly to an audio recording device. The purpose of this session was to minimize potential reactivity to these monitoring devices during baseline and post-intervention sessions. Data collected during this familiarization lesson will not be analyzed. Baseline and post-intervention data were collected from all participating students, regardless of study arm, during and immediately after two 20-min segments of PE lessons. In between these two lessons, teachers received a brief intervention (three experimental arms) or were asked to continue with usual practice (control arm).

**Figure 2 F2:**
[figure not shown]
**MALP study flow chart**
.

### Sample size and power calculation

Lonsdale et al. [11] found a large difference in PA levels between free choice and structured PE lesson conditions (Cohen’s *d* = 1.07). We adopted a conservative approach and estimated a moderate effect size (medium *f* = 0.25) for mixed (between and within-subjects) analysis. Based on this estimation, as well as an estimated correlation of *r* = 0.5 among the repeated measures of PA (*r* = .53 in a previous study [11]), we required a sample of 76 students in order to achieve 95% power, with alpha set at .05. Taking into account the clustered nature of the data, this sample size was multiplied by a correction factor of 1+(*m* - 1)ρ, called the design effect, where *m* is the average cluster size and ρ is the intra-class correlation coefficient [35]. Assuming an *m* of 25 students per class and ρ = 0.1 (estimated based on a previous study [36]), the correction factor is 3.4. As a result, a sample of 258 students (i.e., 76 × 3.4 = 258) was required. To allow for lack of informed parental consent or assent from some students, and to protect against participant attrition across the four teaching conditions, we attempted to increase the sample by 20% and recruit 308 students from 16 PE classes.

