### Randomization

The 16 PE teachers, with their students, were randomly assigned to one of four conditions (three interventions and one control). An independent researcher, blinded to the study hypotheses, performed the allocation after the baseline assessment was administered. Randomization was conducted at the class-level and within schools to control for school characteristics, using a computerized random number generator with blocked randomization scheme (block size = 4). School 1 (Catholic – coeducational), School 2 (Independent – girls only), and School 3 (Independent – coeducational) each provided four classes of students and one class from each school was randomly assigned to one of the four conditions. School 4 and School 5 (two classes each) were both Catholic boys schools. Together, these two schools constituted the final block from which four classes were randomly assigned.

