## Discussion

This cluster randomized controlled trial was designed to evaluate potentially effective motivational teaching strategies in PE with the aim of helping adolescents to have more self-determined motivation for PA, and to be more physically active, both in PE lessons, and beyond. The study design will allow us to compare the effect of three Self-Determination Theory-based teacher motivational strategies on PA levels, motivation, and basic needs satisfaction during PE lessons. The findings from this study will be used to inform effective SDT-based teaching interventions to promote PA in youth.

Our study was among the first to use objective measures of PA along with assessments of PA antecedents in an experimental design that tests the relative effectiveness of Self-Determination Theory-based teaching strategies. Beyond novelty and rigor, strengths of this study include the use of a real-world setting in community-based PE lessons, with professional teachers implementing intervention strategies with their own students in their lessons. Also, the study’s manipulation checks will strengthen our ability to determine how well teachers implemented the intended interventions, which is crucial for making causal inference regarding the relationship between teaching strategies and student PA. An additional strength comes from the use of both “providing” and “free” choice teaching strategy conditions, which will enable us to determine the type or degree of choice needed to impact motivation and PA levels in adolescents.

Alongside study strengths, the following limitations should be noted. Our study sample was limited to teachers and students from Independent and Catholic schools, and results may not be applicable to government-funded school settings. Although our study sample size has been planned with adequate power to detect hypothesized relationships, generalizability to other Independent and Catholic schools could be limited both by the modest sample size and by potential selection bias stemming from the use of only schools whose principals were among the first to participate.

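### The 95% power applies to differences between arms in mean change of about 1.0 to 1.4 SD, not to a moderate, conservative effect

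*Protocol article*

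**What the plan says.** The section on sample size and power starts from an earlier study with d = 1.07 between free-choice and structured lessons. It then says "We adopted a conservative approach and estimated a moderate effect size" and gives the scale as "estimated a moderate effect size (medium *f* = 0.25) for mixed (between and within-subjects) analysis", with "an estimated correlation of *r* = 0.5 among the repeated measures of PA". From these inputs, "we required a sample of 76 students in order to achieve 95% power, with alpha set at .05". The clustering step reads "Assuming an *m* of 25 students per class and ρ = 0.1"; it gives a factor of 3.4, a requirement of 258 students and a target of 308 in 16 classes.

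The design has four arms and two measured lessons. Under Randomization, classes were "randomly assigned to one of four conditions (three interventions and one control"), and under Methods/design, "Baseline and post-intervention data were collected from all participating students". The Hypotheses section predicts larger changes than under usual practice. The limitations paragraph of the Discussion says that "our study sample size has been planned with adequate power to detect hypothesized relationships".

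The article does not translate f = 0.25 into a difference between arms.

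**The concern.** Cohen's f = 0.25 is a conventional medium value when f is the SD of the arm means divided by the SD of the score being analysed. In a repeated-measures interaction test, the same symbol is multiplied up by the number of occasions and by the correlation before it reaches the noncentrality. An f of 0.25 entered there can therefore stand for a much larger difference in change. Change relative to usual practice is what the hypotheses concern.

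The interpretation of the result is at stake. If a strategy shows no clear benefit, a reader who trusts 95% power for a moderate effect will take that as good evidence against a moderate benefit. The design may not support that inference.

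**Working it through.** **Inputs.** f = 0.25, r = 0.5, alpha 0.05, N = 76, assumed class size 25, ICC 0.1, 258 and 308 students, 16 classes (all from the sample size section); 4 arms (Randomization); 2 occasions (Methods/design).

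**1. Reproduce the plan's figure.** For the arm-by-occasion interaction, λ = N·f²·2/(1 − r).
- N = 76: λ = 76 × 0.0625 × 2/0.5 = 19. On F(3, 72), power is 0.959.
- N = 72 gives 0.948. N = 73 is the smallest that passes, and it rounds up to 76 for four equal arms.
- Other tests do not give 76: the two-group interaction needs 54, the four-group within-student main effect 55 to 56, the four-group between-student main effect 210 to 212.
- Design effect: 1 + 24 × 0.1 = 3.4, and 76 × 3.4 = 258.4.

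**2. What f = 0.25 means in that test.** With two occasions, the interaction test is a one-way ANOVA on change scores with λ = N·f_change². So f_change = √(19/76) = 0.50. Equivalently, f_change = 0.25 × √(2/0.5) = 0.50. The SD of a change score is σ√(2(1 − r)) = σ at r = 0.5, so the SD of the four arm mean changes is 0.50 single-lesson SD. At the r = 0.53 cited from the earlier study, the SD of change is 0.97σ, which alters nothing material.

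**3. Gap between extreme arms for f_change = 0.50.**

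| Pattern of mean changes | SD of means ÷ gap | Gap (SD) |
|---|---|---|
| Two arms against two | 0.500 | 1.00 |
| One arm against three | 0.433 | 1.15 |
| Evenly spaced | 0.373 | 1.34 |
| One high, one low, two midway | 0.354 | 1.41 |

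**4. Power for a medium effect on change (f_change = 0.25).**
- Plan's own effective N of 76: λ = 0.0625 × 76 = 4.75; F(3, 72) gives 0.40.
- 16 classes, ICC 0.1, 12 error df (16 − 4):
  - 258 students: 16.1 per class, design effect 2.51, effective N 102.7, λ = 6.42, power 0.41.
  - 308 students: 19.25 per class, design effect 2.825, effective N 109.0, λ = 6.81, power 0.44.
- Same model, other ICCs: 0.27 (ICC 0.2, 258 students) to 0.61 (ICC 0.05, 308 students).
- Baseline adjustment, which divides λ by 1 − r² = 0.75, at ICC 0.1 and 12 df: λ = 8.56 and 9.09, power 0.53 and 0.56.
- Most favourable combination tried (baseline adjustment, ICC 0.05, 308 students): effective N = 308/1.9125 = 161.0, λ = 0.0625 × 161.0/0.75 = 13.4, power 0.75.

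Before clustering, 95% power at f_change = 0.25 needs 279 students, or 280 for equal arms. That is 280 × 3.4 = 952 with the plan's factor.

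**5. Effect of 12 error df on the plan's own effect (f_change = 0.50, ICC 0.1).** λ = 0.25 × 102.7 = 25.7 and 0.25 × 109.0 = 27.3; F(3, 12) gives 0.96 and 0.97.

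**6. One strategy against usual practice (unadjusted change, ICC 0.1, 12 df).** SE = √(2 × (0.1 + 0.9/m)/4) = 0.279 SD (m = 16.1) or 0.271 SD (m = 19.25). Power for 0.5 SD is 38% to 40%. For 80% power the difference must be about 3.05 SE: 3.05 × 0.271 = 0.83 to 3.05 × 0.279 = 0.85 SD.

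**The case against.** The best defence is that nothing was miscalculated. The article names the mixed analysis, states r and uses the conventional label for f = 0.25, and every figure reproduces. That stands: this is a fault in describing the effect, and a reader should not infer an arithmetic error. It does not rescue the adjectives, because the label belongs to the scale of the analysed score, where the ratio is 0.50.

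The comparison with d = 1.07 also needs care. The article does not say which SD standardises it, and in the two-against-two pattern the assumed gap of 1.00 is slightly below 1.07. The comparison is therefore conditional.

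Four stronger readings are tempting, and the document does not support them:

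- **That 72 error df instead of 12 invalidates the 95%.** At the assumed effect and ICC 0.1, power on 12 df is still 0.96 to 0.97, because 258 to 308 students in 16 classes is 16 to 19 per class, not 25.
- **That the trial's power is 40%.** That figure is for an unadjusted change analysis at an ICC of about 0.1. The planned analysis is described only as a linear mixed model, so baseline adjustment is open.
- **That only very large effects are detectable.** A strategy-versus-control difference of 0.83 to 0.85 SD has 80% power at ICC 0.1.
- **That an omnibus test is the wrong basis for the sample size.** Research Questions 1 and 2 ask whether outcomes differ across all four conditions, which is what the interaction tests.

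**Conclusion.** The point holds as a misdescription of what the power covers. The 95% belongs to an SD of 0.50 across arm mean changes, with extreme arms 1.00 to 1.41 SD apart. That is neither moderate nor evidently cautious beside d = 1.07, provided that d uses a comparable SD. For a medium effect on change, power is 0.40 on the plan's own effective sample, 0.27 to 0.61 without adjustment across ICCs of 0.2 to 0.05, and 0.53 to 0.56 with baseline adjustment at ICC 0.1. Even the most favourable combination tried reaches only 0.75.

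These figures assume that moderate means Cohen's medium on the change scale, that the ICC applies to the analysed score, that classes are of equal size, and that error df are 12. The ICCs of 0.05 and 0.2 are my sensitivity values; only 0.1 is in the article. The equivalence of 0.25 and 0.50 needs only the article's two occasions and r = 0.5.

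**What to change.** In the sample size section:

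- Remove the words *conservative* and *moderate*.
- State that the 95% refers to an SD of 0.5 across the arms' mean changes, which is a largest arm difference of 1.0 to 1.4 SD.
- Report power for f = 0.25 on change for the actual 16 classes, with the ICC, error df and any baseline adjustment named. Give it as a range, roughly 0.3 to 0.6 for the main cases above, because a single figure would be falsely precise.
- Add the strategy-versus-usual-practice difference detectable with 80% power: about 0.83 to 0.85 SD at ICC 0.1 with unadjusted change.
- State which SD standardises d = 1.07, or drop the comparison.

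In the Discussion, limit the claim of adequate power to effects of that size.

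The cost is a few sentences. Enrolment, data collection and the planned model stay as they are. The stated power becomes less favourable.

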### Randomization

The 16 PE teachers, with their students, were randomly assigned to one of four conditions (three interventions and one control). An independent researcher, blinded to the study hypotheses, performed the allocation after the baseline assessment was administered. Randomization was conducted at the class-level and within schools to control for school characteristics, using a computerized random number generator with blocked randomization scheme (block size = 4). School 1 (Catholic – coeducational), School 2 (Independent – girls only), and School 3 (Independent – coeducational) each provided four classes of students and one class from each school was randomly assigned to one of the four conditions. School 4 and School 5 (two classes each) were both Catholic boys schools. Together, these two schools constituted the final block from which four classes were randomly assigned.

### Intervention and fidelity check

Prior to the post-intervention PE lesson, each teacher met with a researcher (CL) for approximately 20 minutes to be trained to deliver the assigned motivational strategy. This meeting took place 20–48 hours before the post-intervention lesson. During this meeting, the investigator asked the teacher to share the lesson plan from the baseline lesson or to describe the baseline lesson activities if the lesson plan was not available. The investigator asked the teacher to devise a lesson for the post-intervention PE lesson that was similar in structure to the baseline lesson. He then guided the teacher through a one-page outline of the proposed teaching strategy. This outline included the strategy name, definitions, the rationale behind the strategy, and guidelines for implementation. The teacher had the opportunity to ask questions, and the researcher and teacher discussed plans for strategy implementation in the upcoming lesson.

The researcher trained the teachers randomized to the “relevance” arm (n = 4) to make statements during the PE lesson that explained the rationale behind the activities in the lesson, and made it clear how the activities were relevant to students’ lives. The researcher trained the teachers randomized to the “providing choice” arm (n =4) to provide students with opportunities to make choices from options that were selected by the teacher. In line with meta-analytic evidence regarding the provision of choice [34], teachers were asked to provide between 2–4 opportunities for choice during the lesson. When providing students with an opportunity a choice, teachers were also asked to avoid overburdening students with too many options from which to choose (i.e., ≥ 5). The researcher asked the teachers randomized to “free choice” (n = 4) to provide the students with complete free choice; meaning that equipment would be provided, but the teacher would not provide any instruction. It could be argued that this strategy does not include adequate lesson structure and may undermine perceived competence [37]. Previous research, however, has indicated that complete free choice can increase students’ total PA accumulated during a lesson, relative to standard practice [11]. Therefore, an investigation of potential effects on needs satisfaction, motivation, moderate-to-vigorous PA and sedentary behavior is warranted. The researcher asked teachers randomized to the control condition (n = 4) to continue with their usual practice.

Teachers in all four study arms had their verbal communication audio recorded in baseline and post-intervention lessons. To test the fidelity of the interventions, two independent researchers assessed teachers’ provision of autonomy support. Specifically, the researchers used four items from the Teacher as Social Context Questionnaire [21] to rate the extent to which: (1) “The teacher gave the students choices about how they do the tasks in PE”; (2) “The teacher talks about how the students can use the things they learn in PE”; (3) “The teacher listens to the students’ ideas”. and (4) “It seems like the teacher is always telling the students what to do”.

As indicated in Table 1, compared with the control and “relevance” arms, teachers in the “providing choice” and “free choice” arms were expected to exhibit greater increases in provision of autonomy support from baseline to post-intervention on the first item. Teachers in the “relevance” arm were expected to exhibit larger increases than the other three arms on the second item. The raters hold PhD qualifications in a related discipline (e.g., psychology) and have knowledge of motivational theory applied to physical activity contexts, as evidenced by at least five peer-reviewed publications on the topic. Also, raters were blinded to study hypotheses and teachers’ allocation to the control or experimental arms.

**Table 1 T1:** Motivation strategy conditions

**Intervention arms**	**Description**	**Hypothesized impact on PA****and SDT constructs, relative****to baseline**
Free Choice	Equipment provided, but no instruction by the teacher took place.	Higher PA levels
		Lower sedentary behavior
		Higher autonomy support from teacher (especially perceived choice)
		Higher basic need satisfaction
		Higher self-determined motivation
Providing Choice	Provided options and offered opportunities for students to take initiative.	Higher PA levels
		Lower sedentary behavior
		Higher autonomy support from teacher (especially perceived choice)
		Higher basic need satisfaction
		Higher self-determined motivation
Relevance	Provided rationale and explained relevance of activities	Higher PA levels
		Lower sedentary behavior
		Higher autonomy support from teacher (especially perceived relevance)
		Higher basic need satisfaction
		Higher self-determined motivation
Usual practice	No intervention. Lesson activities conducted without researcher-directed teaching strategies	No change in PA levels
		No change in sedentary behavior
		No change in basic need satisfaction
		No change in self-determined motivation

Note: PA = physical activity, SDT = Self-Determination Theory.

### Outcome measures

Different schools and classes were expected to have PE lessons of varying duration and, due to fatigue, it is possible that MVPA levels at the end of longer lessons could be lower than earlier in the lesson. To standardize across lessons of varying durations, all PA data collection occurred during the first 20 min of teaching time during each lesson for the baseline and post-intervention assessments (i.e., after students had changed their clothes and been fitted with an accelerometer). ActiGraph GT3X accelerometers (ActiGraph; Pensacola, FL) were used to assess PA levels (percentage of time spent in MVPA and percentage of time spent sedentary) of each student in this study. Monitors were synchronized with an external clock and initialized to start recording data in three axes of motion in 1-sec epochs, a minimum of 30 min before and after the scheduled PE lessons. Research assistants helped students place an Actigraph monitor, via adjustable elastic belt, over the right iliac crest, prior to the start of each observed PE lesson, to wear for the duration of lesson. Raw accelerometer counts were uploaded to a lab computer, and saved to a customized Microsoft Excel file. Data outside the recorded start and finish time for given sessions was disregarded. Data were checked for spurious values that did not coincide with the direct observation records; all data between start and finish times for all lessons were included in the analyses. Freedson’s MET prediction equation [38] was used to determine PA intensity, and 100 counts per minute was used as a criterion to determine sedentary time [39].

At the 20-min mark of the baseline and post-intervention lessons, each student completed the four items from the Teacher as Social Context Questionnaire described previously. This version of the questionnaire is designed to measure students’ perceptions of their teachers’ autonomy supportive behavior [21] (e.g., “The teacher gives us choices about how we do the things in today’s class”). Students also completed measures of autonomy need satisfaction [24,40], competence need satisfaction [41], relatedness need satisfaction [42], and controlled and autonomous forms of motivation (Situational Motivation Scale) [43]. Each measure has received empirical support regarding reliability and validity in English-speaking samples of this age group [11,14,21,41-44].

Research assistants, who were senior undergraduate students, conducted all data collection. Research assistants received two hours of data collection training from researchers (CL and RR) who had experience with these data collection techniques. All research assistants were blinded to study hypotheses and cluster allocation (i.e., to intervention or control). Students in each PE class were also blinded to allocation; however, teachers were necessarily un-blinded when they received the intervention (i.e., post-baseline assessment) or learned that they were in the control arm of the trial.

Students’ age, gender, place of birth (Australia or other) and main language spoken in the home (English or other) were collected. A proxy measure of socio-economic status was collected, as students reported their home postcode. This postcode was cross-referenced with census data [45] to determine the economic decile of each student’s home neighborhood.

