**Methods/design:**

This study employed a cluster-randomized controlled trial design. Following a familiarization session, PA levels and hypothesized PA antecedents were measured during a baseline lesson and a post-intervention or control lesson. Teachers (n = 16) and their classes from five secondary schools in Sydney, Australia were randomly assigned into four blocks and instructed to provide one of four 20-min lesson teaching strategy conditions: (1) explaining the relevance of activities; (2) providing choice from PA options selected by the teacher; (3) providing equipment and free choice of activities; or (4) usual practice. The primary outcomes were lesson time spent in moderate-to-vigorous PA, and motivation towards the lesson. Secondary outcomes were perceptions of teacher behavior, psychological needs satisfaction, and lesson time spent in sedentary behavior. PA and sedentary behavior were measured during baseline and post-intervention lessons with waist-mounted Actigraph GT3X accelerometers. Teacher behavior, psychological needs satisfaction, and motivation were assessed via questionnaires at the end of each lesson. Linear mixed-model analyses will be run on all outcomes, with students nested within teachers as a random effect.

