### Theoretical framework

The current study is based on Self-Determination Theory (SDT) [16,17] which has been widely applied to a variety of life contexts, including education [18], sport [19], exercise [20], and PE [11,21]. According to SDT tenets, social-contextual factors (e.g., teaching strategies used by PE teachers) can affect individuals’ motivation by satisfying (or undermining) three key psychological needs: 1) autonomy: the need to self-endorse activities and beliefs; 2) competence: the need to effectively interact with one’s environment and yield desirable outcomes; and 3) relatedness: the need to feel connected and accepted by significant others [16,17].

In the context of PE, when teachers use motivational strategies that satisfy key psychological needs, students will feel more self-determined to participate in PE, and thus will be more physically active during lessons [11]. Motivational strategies that support student needs include: (1) “choice”: providing students with the opportunity to make decisions about the activities they undertake during lessons; (2) “relevance”: providing a rationale and explaining to students the relevance of an activity; (3) “acknowledgement”: acknowledging students’ difficulties when learning skills; and (4) “feedback”: providing feedback using praise for students’ effort and improvement. Previous studies have shown that these strategies can satisfy the three key psychological needs in the PA context, and are essential to well-being, learning, and the development of autonomous forms of motivation (e.g., intrinsic motivation) [22-24].

In contrast, teachers’ motivational strategies that undermine student autonomy (e.g., controlling strategies such as discouragement of student initiative, overt teacher control, conditional student acceptance and praise) may thwart students’ psychological needs and thereby result in controlling forms of extrinsic motivation or lack of motivation, anxiety, and poor psychological adjustment [25]. In the PE context, such dysfunctional motivational strategies may reduce PA levels. Experimental research in the contexts of education [26] and PA promotion in adults [27] has supported these theoretical predictions and a recent study showed that providing children (aged 8–12) with choice increased physical activity in a laboratory setting [28].

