### Aims of the study

The aim of the current project was to investigate the relative effects of three motivational teaching strategies on motivation and PA levels during Year 8 PE lessons. Specifically, we sought to use a cluster-randomized controlled trial to test the effectiveness of three SDT-based motivational teaching strategies, in comparison with usual teaching practices. Understanding which strategies have the greatest impact on PA may allow for the development of effective interventions to increase long-term student motivation and PA during PE lessons, and potentially beyond PE.

There were three main research questions:

Research Question 1: Do students differ across the three motivational teaching strategy conditions and control (usual practice) teaching condition with regard to moderate-to-vigorous PA (MVPA) (primary outcome) and sedentary behavior (secondary outcome) during PE lessons?

Research Question 2: Do student motivation towards PE lessons (primary outcome), needs satisfaction, and perceptions of teacher behavior (secondary outcomes) differ across the three motivational teaching strategy conditions and the control (usual practice) teaching condition?

Research Question 3: Are the effects of motivational teaching strategies on PA and sedentary behavior mediated by teachers’ autonomy supportive behavior and students’ needs satisfaction and motivation during lessons? (See Figure 1).

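### Student-reported mediators and the activity outcome cover the same 20-minute segment, so Research Question 3 cannot tell motivation driving activity from activity driving reported motivation

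*Protocol article*

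**What the plan says.** Activity outcome. The protocol article, Outcome measures, states that "all PA data collection occurred during the first 20 min of teaching time during each lesson for the baseline and post-intervention assessments".

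Student reports. The same section continues: "At the 20-min mark of the baseline and post-intervention lessons, each student completed the four items" of the perceived-teacher-behavior scale. It then adds that "Students also completed measures of autonomy need satisfaction", along with competence, relatedness and situational motivation, and gives no other time point. The main Methods/design text agrees: data came "during and immediately after two 20-min segments of PE lessons". The Abstract puts it slightly differently: "Teacher behavior, psychological needs satisfaction, and motivation were assessed via questionnaires at the end of each lesson".

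The question asked of these data. Research Question 3 (Aims of the study) asks whether effects on activity and sedentary behavior are "mediated by teachers’ autonomy supportive behavior and students’ needs satisfaction and motivation during lessons". Hypothesis 7 points to the same paths through Figure 1. The Theoretical framework gives the direction: "students will feel more self-determined to participate in PE, and thus will be more physically active during lessons".

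Other relevant facts. Teachers' speech was audio recorded in both lessons. Two independent raters, blinded to hypotheses and allocation, scored autonomy support from it (Intervention and fidelity check). The limitations in the Discussion cover school type, sample size and school selection, but not the timing of the mediators.

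**The concern.** A mediation claim needs the mediator to act on the outcome. Here the student-reported mediators are read once after allocation, when the activity window has closed, and they describe that same window. No post-allocation student report precedes the activity it is meant to explain, and no activity is measured after the report.

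A rival account is easy to state. In the free-choice arm the teacher gives no instruction, which may raise activity directly. Students who have just been active may then report more competence or motivation. The data from this account and from the hypothesized one could look alike. This example fits the free-choice arm best; the relevance arm adds explanation rather than removing it.

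At stake is the answer to one of the three main research questions. The article calls needs satisfaction and motivation antecedents of activity and, under Implications of study findings, expects understanding of them to be useful to researchers and policy makers.

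**Working it through.** The plan gives no figure on this point, so there is none to reproduce. The check has three parts.

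**1. Order of measurement in the post-intervention lesson**

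- Minutes 0 to 20: MVPA and sedentary time by accelerometer (Outcome measures).
- Minute 20: student questionnaire (Outcome measures). Methods/design places it immediately after the segment; the Abstract places it at the end of the lesson. On every reading it does not precede the activity.
- Reference period of the reports: the lesson just experienced. The example item asks about that day's class, and the hypotheses concern needs and motivation during lessons.
- Measured lessons after allocation: one.

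The two variables therefore describe the same period, and the report is given at its close.

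**2. What randomization identifies**

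- Strategy to activity: identified (Research Question 1).
- Strategy to reported needs and motivation: identified (Research Question 2).
- Direction of the link between motivation and activity: not identified. The baseline lesson supplies earlier values of both and can remove prior differences, but it does not order them within the later lesson.

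**3. Illustration of size**

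The assumptions are not from the documents: no true mediation, and a report M that depends only on activity. Let X be the strategy (0 or 1), d its effect on activity in SD units, and r the within-arm correlation.

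- PA = d·X + e, with var(e) = 1.
- M = r·PA + √(1 − r²)·u, with var(u) = 1, so the within-arm variance of M is r² + (1 − r²) = 1.
- Path a (M on X) = r·d.
- Path b (PA on M, given X) = r / 1 = r.
- Apparent indirect effect = a·b = r²·d. Total effect = d. Apparent mediated share = r².

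| r | r² |
|---|---|
| 0.3 | 9% |
| 0.5 | 25% |
| 0.7 | 49% |

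The scaling matters. If 0.3, 0.5 and 0.7 are instead slopes of M on PA with unit residual variance, the share is r²/(1 + r²): 0.09/1.09 = 8%, 0.25/1.25 = 20%, 0.49/1.49 = 33%. A simulation with that scaling (258 independent students, two arms, d = 0.5, 4,000 runs per setting) gave the same shares. Both mediation paths were significant at the 0.05 level in 21%, 42% and 63% of runs, although no mediation existed. Clustering and the baseline lesson are left out, so these rates show the direction of the problem, not its size in this trial.

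**The case against.** The strongest objection is that the time of recording is not the time of the construct. Students report how they felt during the segment, and a student can hardly be asked before a lesson how motivated he or she was in it. Stopping midway to ask would disturb the activity outcome. This stands. A reader might infer that the trial measured activity first and motivation second, the reverse of the hypothesis. The documents do not support that: the reports are retrospective, so the accurate description is concurrent measurement with an ambiguous direction. The ambiguity remains, because a retrospective report can be colored by the activity just finished.

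Second, Research Question 3 names teachers' autonomy-supportive behavior, not only students' perceptions of it, and blinded audio ratings can measure it. This also stands. It would be wrong to extend the point to the whole of Research Question 3.

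Third, the mediation model may sit in an analysis plan that is not shown. That is a fair answer to any complaint about a missing model, and none is made here. A reader might also infer that the plan commits the authors to presenting an indirect effect as proven mechanism; the article states a question and a hypothesis, no more. The timing, however, is fixed in the article, and no model for these data supplies the missing order without an untestable assumption.

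Fourth, r is not in the documents and the illustration assumes purely reverse causation. That is correct, and the percentages should be read only in that light.

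**Conclusion.** The point holds for student-reported needs satisfaction and motivation, and for perceived teacher behavior if that is used as the mediator. For these paths, Research Question 3 and hypothesis 7 cannot separate motivation driving activity from activity driving reported motivation. The timing rests on three consistent places in the article.

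The size is unknown. Under the assumed no-mediation model the apparent share is r², or 9% to 49% for r between 0.3 and 0.7; this is not an estimate of bias in this trial. Research Questions 1 and 2, and with them both primary outcomes, are unaffected. The link through audio-rated teacher behavior is less exposed. The matter is a cheap improvement to what may be concluded on one main question, not a flaw in the randomized comparisons.

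**What to change.** The lessons took place in 2011, so the timing cannot change. The analysis is still described as planned, which leaves room for four changes:

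- Restate the student-reported paths in Research Question 3 and hypothesis 7 as associations consistent with the model, rather than as mediation.
- Add the timing of the questionnaires relative to the activity window to the limitations in the Discussion.
- Report the reverse-path model (strategy to activity to needs and motivation), adjusted for the baseline lesson, beside the planned one. It will not decide the direction, but it shows whether the data are equally compatible with the rival account.
- Use the blinded raters' audio score as the teacher-behavior mediator. State that it varies only across 16 teachers and will be imprecise.

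An analysis of activity in the minutes after the questionnaire is tempting, since monitors were worn for the whole lesson, but it is not recommended. Outcome measures limits activity data collection to the first 20 minutes and disregards data outside the recorded session times, and the Abstract defines the strategies as 20-minute conditions.

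The cost is some wording, one extra model on data already collected, and a weaker claim about mechanism.
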